### Offender interviews

Previous research indicates that the employment rate of offenders released from prison is 25 % [9]. The IPS literature consistently demonstrates that participation in IPS doubles the percentage of people in paid employment [41]. However, this excludes offenders who, for reasons cited earlier, face additional obstacles to employment. Therefore, in consideration of previous IPS research and the experience of the research team, an estimated hypothesis for the primary outcome is that 40 % of those on IPS will work at least one day in paid employment compared with 25 % for those who do not take part in IPS: at least eight of the intervention group of 20 will obtain work, as compared to five of the control group. A 15 % net increase in the competitive employment rate is both clinically and socially meaningful as not only would this reduce the range of costs to society that are associated with this population, but according to previous findings employment can have a positive impact on each individual’s life satisfaction and their mental health, especially if this is sustained [37, 38].

As there is no randomisation with regards to who takes part in IPS and who does not take part in IPS, motivation to gain employment will be measured, making it possible to control for the effect of differences in motivation on outcomes using logistic regression.

Given that the majority of recruitment and consent will be taken within prison the research team estimate that most (80 %) of those approached to participate in the research will take part. Furthermore, as not everyone who is approached will take part in the research, even though they may take part in IPS, it is believed that 36 people within each group will need to be approached.

### Staff interviews

A total of around 20 staff participants will be recruited in order to gain a thorough insight and range of perspectives into how the intervention works, develops, is delivered, and fits into the CJS. Only National Offender Management Service (NOMS) staff involved in some way with the intervention and/or overall involvement with participants will be interviewed. Estimated N = 10.

Other key stakeholders and agencies involved in the overall care of participants and/or the delivery of IPS, such as employment specialists, will be interviewed once or twice only to gain an understanding of their perspective of the intervention. Interviews with such staff will occur with an estimated N = 10.

### Data collection

#### Validated measures

All of the measures seen in Table 1 are highly validated and will assess the mental health, social stability, including social network, and the motivation of each participant. Each measure is self-administered, however, the researcher will help each participant where necessary. The TAG is already routinely present on each client’s file and will be completed twice by staff who know the participant well. Each set of questionnaires will take around 30 minutes to complete.

**Table 1 Tab1:** Data collection measures and time frame for offender participants

*Measure*	*Baseline*	*6 months*	*12 months*
Threshold Assessment Grid (TAG) [42]		*√*	*√*
General Health Questionnaire-12 (GHQ-12) [43, 44]	*√*	*√*	*√*
Brief Symptom Inventory-18 (BSI-18) [45, 46]	*√*	*√*	*√*
Manchester Short Assessment of Quality of Life (MANSA) [47]	*√*	*√*	*√*
Social Network Analysis (SNA) [48]	*√*		*√*
Motivation and Readiness to Work scale (MTW) [49]	*√*	*√*	*√*
Reconviction Analysis			
Semi-structured Interview	*√*	*√*	*√*

#### Semi-structured interviews

Semi-structured interviews will last between 30 to 60 minutes, a total of less than 90 minutes per offender. The researcher will follow a topic guide (available from the authors on request). It is also important to note that participants may be recalled to prison for a number of reasons other than reoffending, therefore, this will be taken into account and questions and/or prompts within this topic guide will be asked as appropriate.

Interviews will be carried out to gain an understanding of the individuals’ motivations and expectations of the IPS service and to understand how the intervention is working. Interviews will also generate data concerning the impact of IPS and/or any employment gained on the core areas under investigation- mental health, social stability, and recidivism.

All participants will initially be asked questions about their offending behaviour. Participants who have reoffended will be given an opportunity to discuss their offending behaviour and the reasons for it, within the semi-structured interviews. Those who do not reoffend will be asked questions about what they believe has helped them to desist from criminal behaviour.

The initial and subsequent interviews will take place in prison and then in the community, respectively, however, this may vary depending on referral and participant location at time of interview.

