### Rigour and reliability

RE is unique from other research methods as it is able to isolate mechanisms of change within an intervention [50]. Different stakeholders will have diverse information, understandings, and divisions of expertise about how IPS has and may work. RE ensures that the correct questions are asked to the right ‘experts’ in each area under examination. This can then allow for an examination of the mechanism (s) which create new and/or continuous behaviour (s) concerning the research areas.

It is anticipated that by examining employment outcomes and the impact being involved in IPS and/or employment has and had on a client’s overall mental health, re­offending, and social stability, in comparison to those not on IPS, how to best adapt IPS within the justice system can be understood. By examining individual circumstances, mechanisms, and the context (CMOs), as well as all data collected from both ‘positive’ and ‘negative’ cases regarding who gains employment, ways in which the intervention can be improved within different contexts can then be proposed.

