### Qualitative data

Interviews with clients and key stakeholders will create text that will be analysed through Thematic Analysis [53]. Themes will be recorded and refined through a systematic process using NVivo software. The researcher will identify codes in the interview material. Codes are the basic element of the data that illustrate information that is of interest to the analyst [54]. An initial list of codes will be compiled and then organised into overarching themes. A thematic summary once created can be refined through further interviews and feedback to categorise themes at each stage of outcomes produced [55].

Interviews and observations with employment personnel will be developed into themes of how IPS has developed and/or been modified within the CJS. Interviews and observations with employment personnel will also generate information into what works, and what doesn’t work, with what particular population and client.

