By examining Police National Computer (PNC) data the proven one year re­offending rates of individuals who took part in IPS will be made clear. Specifically, whether any offence has been committed and whereby a conviction, caution, warning or reprimand was received within the one year follow up and six month waiting period [56]. This will also give an indication of the severity and regularity of reoffending in comparison to each individual’s own previous offending behaviour.

To generate stronger findings that go beyond whether an individual offends or not and how this compares to their previous offence history it is important to determine what would have happened to the participants on IPS should they not have taken part, an estimate is needed. This estimate is known as the ‘counterfactual’ [57] and will enable a comparison in reoffending rates of those who took part in IPS with those who did not. Making this comparison ensures that the only major difference in characteristics between both groups is the IPS intervention. In order to isolate the effects of IPS in this way those on IPS will be matched on key factors which influence reoffending with a comparator group (No IPS). A logistic regression, Propensity Scored Matching (PSM), will be utilised to carry out this comparison.

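### Follow-up interview questions on offending depend on whether the participant reoffended, so the interview themes can create or inflate an apparent link between work or IPS and desistance

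*Protocol article*

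**What the plan says.** All points are in the protocol article.

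- **Semi-structured interviews**, common opening: "All participants will initially be asked questions about their offending behaviour".
- Same section, if the participant reoffended: "Participants who have reoffended will be given an opportunity to discuss their offending behaviour and the reasons for it".
- Same section, if not: "Those who do not reoffend will be asked questions about what they believe has helped them to desist from criminal behaviour".
- Same section, use of the material: "Interviews will also generate data concerning the impact of IPS and/or any employment gained on the core areas under investigation". Recidivism is one of the core areas then listed.
- Same section, format: "The researcher will follow a topic guide (available from the authors on request"). The guide itself is not reproduced.
- **Table 1**: interviews at baseline, 6 and 12 months.
- **Qualitative data**: "Interviews with clients and key stakeholders will create text that will be analysed through Thematic Analysis".
- **Quantitative data**: interview themes also supplement every research question. The list under Research questions includes the effect of IPS on reoffending rates.
- **Reconviction analysis** and **Quantitative data**: the reoffending effect is assessed separately, from Police National Computer (PNC) records and a matched no-IPS comparator. An offence counts if a sanction was "received within the one year follow up and six month waiting period".

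**The concern.** The interview branches on the outcome it is meant to help explain. As described, the helping factors are sought from those who did not reoffend, and the reasons for offending from those who did. The one question stated as common to all is about offending behaviour, not about what helped or hindered.

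A Realistic Evaluation needs the same mechanism looked for in cases that went well and cases that went badly. If a mechanism is asked about in one outcome group and must be volunteered in the other, a difference in how often it appears may reflect the questioning. At stake is the qualitative account of why IPS or work does or does not reduce reoffending. The article presents that account as going beyond hypothesis testing to causal explanation.

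**Working it through.** There is no stated figure to reproduce, so the check has three parts.

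**1. The passages side by side.**

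| Topic | Reoffended | Did not reoffend |
|---|---|---|
| Offending behaviour | asked | asked |
| Reasons for offending | stated | not stated |
| What helped to desist | not stated | stated |
| Impact of IPS or work | general interview topic | general interview topic |

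The middle two rows are asymmetric by outcome and the last row partly offsets them. The Rigour and reliability section does compare positive and negative cases, but these are "cases regarding who gains employment, ways in which the intervention can be improved within different contexts can then be proposed". They are defined by employment, so they do not balance the questions across reoffending status.

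**2. Timing.** The record outcome needs 12 months of follow-up plus a 6-month wait: 12 + 6 = 18 months. The follow-up interviews are at 6 and 12 months, so the complete record outcome cannot set the branch at either. The article does not say how status is established at interview. Self-disclosure is a reasonable inference, but only that. On that inference, some people with undisclosed or not yet proven offences would get the desistance questions.

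**3. An illustration with no true link.**

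From the article: 20 + 20 = 40 participants; employment (40% + 25%)/2 = 32.5%, unrelated to reoffending.

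Assumed, not in the article: reoffending 30% or 50%; probability q of naming work or IPS as helpful when asked, 20% to 60%; probability u of naming it when not asked, 5% to 20%.

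Expected odds ratio, desisters against reoffenders: OR = q(1 − u) / [u(1 − q)].

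- q = 0.20, u = 0.10: (0.20 × 0.90)/(0.10 × 0.80) = 0.18/0.08 = 2.25
- q = 0.60, u = 0.05: (0.60 × 0.95)/(0.05 × 0.40) = 0.57/0.02 = 28.5
- q = u = 0.20: (0.20 × 0.80)/(0.20 × 0.80) = 1.0

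Share of 2,000 simulated studies in which a two-sided Fisher exact test at 0.05 found a false association:

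| q | u | OR | 30% reoffend | 50% reoffend |
|---|---|---|---|---|
| 0.20 | 0.05 | 4.75 | 7% | 18% |
| 0.20 | 0.10 | 2.25 | 4% | 8% |
| 0.20 | 0.20 | 1.0 | 3% | 3% |
| 0.40 | 0.05 | 12.67 | 58% | 72% |
| 0.40 | 0.10 | 6.0 | 38% | 52% |
| 0.40 | 0.20 | 2.67 | 15% | 21% |
| 0.60 | 0.05 | 28.5 | 93% | 97% |
| 0.60 | 0.10 | 13.5 | 83% | 91% |
| 0.60 | 0.20 | 6.0 | 57% | 69% |

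Tested instead on recorded employment against recorded reoffending, the same simulated studies gave a false association in about 2% to 4% of runs in every scenario. The row with q = u also shows the position after the fix: when both groups get the same question and name work or IPS equally often, the OR is 1.0 and the false-association rate about 3%.

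The test only gauges how visible the artefact could be. The article plans thematic analysis, not counts of mentions.

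**The case against.** The strongest reply is that the wording is a short summary of a topic guide that is not shown, and an article may leave interview detail to it. Nothing says that reoffenders are never asked what helped. The format is semi-structured, and the impact of IPS and work is an interview topic for participants generally. This limits the claim but does not remove it: the article states the branching rule itself, so the point is not about a missing detail.

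Three stronger readings are tempting, and the documents do not support them.

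- *A spurious link is bound to appear.* The desistance question is open and names neither IPS nor work. Reoffenders can cite lost work or failed support among their reasons. Where unprompted naming equals prompted naming, the odds ratio is 1.0. Scoring reoffenders as zero because they were not asked, with 60% of desisters naming work or IPS, gives a gap of 60 points. That is a hypothetical upper bound on assumed inputs.
- *The wording favours IPS over no IPS.* The split is by outcome, not by study group. Desisters in both groups get the same question.
- *The estimated effect on reoffending is biased.* That estimate comes from PNC records and matching, which the interview questions cannot touch.

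It is also fair to object that classifying participants by PNC alone would place self-disclosed but unproven offending among the desisters. That stands, and the fix allows for it.

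**Conclusion.** The concern holds for the interview evidence on recidivism and no further. The article states an outcome-dependent branch and uses the answers to inform how IPS and work affect reoffending. Helping factors can therefore be over-represented among desisters and barriers among reoffenders.

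The size cannot be derived from the documents. The illustrative odds ratios of 2.25 to 28.5, and false-association rates of about 4% to 97%, rest wholly on the assumed naming and reoffending rates and on being asked raising the chance of naming. The PNC analysis addresses whether reoffending differs. It cannot repair the qualitative account of why. The point is worth settling before follow-up interviews, because uneven questioning cannot be undone afterwards.

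**What to change.** Amend the Semi-structured interviews section and the topic guide as follows.

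1. At 6 and 12 months every participant, IPS or no IPS, is asked the same core questions: what helped to avoid offending, what made offending more likely, and what part work or employment support played.
2. Outcome-specific probes come after that core.
3. When themes are compared by reoffending status, use the PNC outcome once it is available, show self-reported status alongside it, and do not rely on the interview branch alone.

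The article does not make clear whether the matched no-IPS comparator is the interviewed no-IPS group. If it is not, the PNC look-up for item 3 must also cover the interviewed controls. The consent described under Ethics and consent already asks for access to criminal records.

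The cost is a topic-guide edit, a sentence or two in the protocol and a few more minutes per interview. Those minutes must fit the stated total of less than 90 minutes per offender. If that total spans the three interviews in Table 1 at the stated minimum of 30 minutes each, 3 × 30 = 90 already reaches it, so the core should replace existing questions or the limit should be clarified.

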### Reconviction analysis

A sample of similar size matched on criteria that influence reoffending, will be compared with the study participants to determine the probability of reconviction with and without IPS involvement. This ‘reconviction analysis’ will also involve comparisons between the two groups on new index offence, sentence length, and overall circumstances.

### Key stakeholders and observations

Semi-structured interviews will take place with employment personnel on two occasions, once when more than five clients have built up on their caseload and once at the end of the project. Interviews will be conducted with all three employment specialists. This will help to understand their role, decisions they make, and the possible day to day barriers that they are faced with to gain competitive employment for clients.

The researcher will also need to be in contact with employment specialists to understand what their role with this new population involves. Observations will occur with each employment specialist for a three to four week period, two to three days per week. The researcher will write up notes after each day observing.

Semi-structured interviews with other key stakeholders involved in the intervention and/or the overall care of participants will be taken at the six and 12 month points where possible. Interviews with employment personnel and other key stakeholders will also both provide an overall context and ‘logic of the stakeholder’ [50]. That is, an understanding of how the service begun, has developed, where it is now, and how it may need to be adapted.

### Fidelity

To permit systematic evaluation of IPS interventions it was essential that a method be developed for assessing adherence to the IPS principles as well as differentiating from programmes that stray from the model. A fidelity scale does just this and could be described as “a psychometrically sound method for determining the degree to which a specific programme meets the standards for a programme model” [51], p. 384. Therefore, a key component in the examination of the IPS intervention and a measure that also provides a detailed operational description and critical ingredients of the IPS model is the 25-item IPS Fidelity Scale (IPS-25) [52].

The IPS intervention has now been running for several months, therefore, a self-assessment fidelity review for the service is due to take place in April 2015. This will be followed by an external review six months after the research begins. The Centre of Mental Health, London, and Shropshire County Council will be organising this process. These fidelity scores can then be integrated into the research analysis when examining employment outcomes through providing adherence to the IPS model during the development of IPS, and when the research data was being collected.

### Analysis

As the research design is RE; both the qualitative and quantitative methods will be applied to the data prior to final interpretations to understand what works, for whom and under what circumstances.

### Rigour and reliability

RE is unique from other research methods as it is able to isolate mechanisms of change within an intervention [50]. Different stakeholders will have diverse information, understandings, and divisions of expertise about how IPS has and may work. RE ensures that the correct questions are asked to the right ‘experts’ in each area under examination. This can then allow for an examination of the mechanism (s) which create new and/or continuous behaviour (s) concerning the research areas.

It is anticipated that by examining employment outcomes and the impact being involved in IPS and/or employment has and had on a client’s overall mental health, re­offending, and social stability, in comparison to those not on IPS, how to best adapt IPS within the justice system can be understood. By examining individual circumstances, mechanisms, and the context (CMOs), as well as all data collected from both ‘positive’ and ‘negative’ cases regarding who gains employment, ways in which the intervention can be improved within different contexts can then be proposed.

### Qualitative data

Interviews with clients and key stakeholders will create text that will be analysed through Thematic Analysis [53]. Themes will be recorded and refined through a systematic process using NVivo software. The researcher will identify codes in the interview material. Codes are the basic element of the data that illustrate information that is of interest to the analyst [54]. An initial list of codes will be compiled and then organised into overarching themes. A thematic summary once created can be refined through further interviews and feedback to categorise themes at each stage of outcomes produced [55].

Interviews and observations with employment personnel will be developed into themes of how IPS has developed and/or been modified within the CJS. Interviews and observations with employment personnel will also generate information into what works, and what doesn’t work, with what particular population and client.

### Quantitative data

To determine whether there was a significant difference between those who took part in IPS and those who did not, concerning whether competitive employment was gained, a Chi-square analysis will be carried out at the six and 12 month intervals. Similarly, a logistic regression will also be carried out at these intervals in order to control for a participants’ motivation to work and assess covariates (e.g. age, gender, criminality) between both groups. Motivation to work will be controlled for during all comparisons, as the decision to seek employment is a personal choice.

Questionnaires pre and post IPS will be analysed using statistical independent sample t­tests, using a Statistical Package for the Social Science (SPSS) software, to determine whether overall significant improvements exist within mental health and social stability between those who did, and those who did not take part in IPS. A case by case examination of client yes/no responses in interviews, social stability measures (job contract and income, accommodation, social network etc.), and structured aspects within social stability questionnaires will be examined in conjunction with all other data, such as themes gained from interviews, to supplement all research questions and to make improvements and recommendations concerning IPS. Unemployment rates, jobs created data, fidelity to the IPS model and any changes in crime rates for particular areas will also be taken into account when examining results.

Descriptive data will be produced to meet the additional secondary outcomes; employment outcomes achieved. All other structured information from the relevant validated measures will be examined case by case for patterns of change amongst those who were part of IPS in comparison with those who were not part of IPS. Appropriate statistical analyses will account for any attrition variation between the IPS and no IPS control condition across the three data collection points. Missing data will also be excluded using the appropriate statistical techniques.

By examining Police National Computer (PNC) data the proven one year re­offending rates of individuals who took part in IPS will be made clear. Specifically, whether any offence has been committed and whereby a conviction, caution, warning or reprimand was received within the one year follow up and six month waiting period [56]. This will also give an indication of the severity and regularity of reoffending in comparison to each individual’s own previous offending behaviour.

To generate stronger findings that go beyond whether an individual offends or not and how this compares to their previous offence history it is important to determine what would have happened to the participants on IPS should they not have taken part, an estimate is needed. This estimate is known as the ‘counterfactual’ [57] and will enable a comparison in reoffending rates of those who took part in IPS with those who did not. Making this comparison ensures that the only major difference in characteristics between both groups is the IPS intervention. In order to isolate the effects of IPS in this way those on IPS will be matched on key factors which influence reoffending with a comparator group (No IPS). A logistic regression, Propensity Scored Matching (PSM), will be utilised to carry out this comparison.

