### Primary and secondary outcome measures

The primary outcome measure for the study is:

Employment gained in a competitive market through the IPS intervention (yes/no).

The secondary outcome measures for the study are:

Mental health, motivation to work, social stability, admissions to a psychiatric hospital, and offending behaviour

This will be assessed at 6 and 12 month intervals. The following information will also be collected where relevant:Time (days) until first competitive employmentJob tenure of competitive employment (hours/days/weeks/months worked from start of IPS)Job stability (working hours/contract gained)Income from employment

Leaving the study for any reason will be measured to assess any bias in the results.

Participant medical records­ hospitalisations, and the reasons for these, will be sought to fully understand the primary and secondary outcomes. Previous hospitalisations predict and increase the chance of future hospitalisation [39] and therefore may interrupt employment or the potential to gain employment during the study.

This medical information will also be very important when examining the mental health and motivation to work of participants throughout the study. By understanding if the participant has had any very recent previous and current hospitalisations, and why, the researcher can control for how this may mediate time until employment, participant dropouts, job tenure, and hours worked.

Information will also be sought from the participants’ prison records. Prison records would reveal any history of offending, index offence information, and the duration of sentence/community order. This information will also be important when examining any barriers a participant may have had when seeking competitive employment.

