## Methods/Design

### Sample size and power

This is a novel piece of research examining how IPS works and develops within a criminal justice setting by means of a Realistic Evaluation (RE). It will yield valuable information for future studies, including the rates of recruitment and retention of participants, as well as the variation in the outcome measures, which is needed to undertake sample size calculations. The current sample size has been determined by the time and resources available: 20 (IPS) and 20 (No IPS) will have a power value of .60 and a critical z score = 1.645 [40] 1.

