## Discussion

The study will be carried out across a wide geographical area. A total of eight sites, seven prisons and one probation area are eligible to provide referrals to the study, including both people who do and do not want help to find competitive employment via the IPS service. This will therefore involve conducting research within the demands of a criminal justice setting, with a population many of whom have chaotic lifestyles.

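### The chi-square and t-tests cannot meet the plan's rule that motivation is controlled in every comparison, and nothing says whether the unadjusted or the adjusted employment analysis decides

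*Protocol article*

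**What the plan says.** Under Quantitative data, the significance question on competitive employment is given to a chi-square: "a Chi-square analysis will be carried out at the six and 12 month intervals". The next sentence adds a logistic regression at the same time points, to control for motivation and to assess covariates such as age, gender and criminality. The section then lays down a general rule: "Motivation to work will be controlled for during all comparisons, as the decision to seek employment is a personal choice". Mental health and social stability are to be compared between the groups with independent-samples t-tests.

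On how the groups arise, Offender interviews says that IPS participation is not randomised and names logistic regression as the means of dealing with differences in motivation. Principal inclusion criteria requires that a participant was offered IPS support. The Discussion describes the referrals as "including both people who do and do not want help to find competitive employment via the IPS service".

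The hypothesis for the IPS group, under Offender interviews, reads "40 % of those on IPS will work at least one day in paid employment". For the control group the assumed rate is 25%. The 15-point difference is called meaningful: "A 15 % net increase in the competitive employment rate is both clinically and socially meaningful". Table 1 schedules the motivation scale (MTW) at baseline, 6 and 12 months.

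**The concern.** The rule and the tests cannot both stand. A chi-square on a 2x2 table has no place for a covariate, and neither has an independent-samples t-test. If motivation is controlled in every comparison, these tests cannot be the basis of any conclusion. If they are, the rule is broken.

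This matters because the groups differ, at least in part, by whether people want help to find work, which may itself affect whether they find it. An unadjusted comparison credits any such difference to IPS. The article recognises the threat and plans an adjusted model, but does not say whether that model or the chi-square answers the primary question. With two analyses at two time points, four results are available. They may disagree, and the more favourable could be reported as the finding.

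**Working it through.** **The plan's own figure.** Sample size and power states that "20 (IPS) and 20 (No IPS) will have a power value of .60 and a critical z score = 1.645". With 40% vs 25% and 20 per group, the usual two-proportion formula at z = 1.645 gives power 0.26, and exact enumeration of the test gives 0.27. The stated 0.60 does not reproduce from these rates. A footnote to that sentence is not shown and may carry other inputs. Nothing below depends on 0.60; the 0.27 is used only as a yardstick.

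**Inputs from the article.** Control rate 25% (5 of 20); target rate 40% (8 of 20); 20 per group; critical z = 1.645.

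**Inputs that are assumptions.** The article gives neither the motivation gap between the groups nor its link to employment. I take a gap d of 0.3, 0.5, 0.8 or 1.0 SD and an odds ratio (OR) for work of 1.5, 2 or 3 per SD of motivation. The IPS effect is set to zero.

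**Model.** Motivation M is normal with SD 1 and mean +d/2 in the IPS group and -d/2 in controls. Then logit P(work) = a + ln(OR) x M, with a chosen so that controls average 25%. The spurious gap is the average P(work) in the IPS group minus 25%.

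Example, d = 0.8 and OR = 2: ln(2) = 0.693 and a = -0.932. The IPS group averages 35.6%, so the gap is 35.6 - 25 = 10.6 points.

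**Rejection rate.** Sum the binomial probabilities of all pairs (x, y), each 0 to 20, for which z = (x/20 - y/20) / sqrt[p(1 - p) x 2/20], with p = (x + y)/40, exceeds 1.645 (one-sided), or for which |z| exceeds 1.96 (two-sided 0.05).

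| Gap d (SD) | OR per SD | Spurious gap (points) | Rejects at z = 1.645 | Rejects at two-sided 0.05 |
|---|---|---|---|---|
| 0.3 | 1.5 / 2 / 3 | 2.3 / 3.7 / 5.4 | 7 / 9 / 11% | 6 / 6 / 7% |
| 0.5 | 1.5 / 2 / 3 | 3.9 / 6.4 / 9.3 | 9 / 12 / 16% | 6 / 8 / 10% |
| 0.8 | 1.5 / 2 / 3 | 6.3 / 10.6 / 15.6 | 12 / 18 / 28% | 8 / 12 / 19% |
| 1.0 | 1.5 / 2 / 3 | 8.0 / 13.5 / 19.9 | 14 / 24 / 37% | 9 / 16 / 27% |

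Yardsticks from the same enumeration: with a true null (25% vs 25%) the test rejects 5% of the time either way. With 40% vs 25% it rejects 27% at z = 1.645 and 18% at two-sided 0.05.

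**Cross-check with a yes/no motivation variable.** Spurious gap = (share motivated on IPS - share motivated in controls) x (work rate if motivated - work rate if not). With 90% vs 30% motivated and work rates of 42.5% vs 17.5%, the gap is 0.60 x 0.25 = 15 points, and controls work at 0.3 x 42.5% + 0.7 x 17.5% = 25%. With 70% vs 50% motivated, a 15-point gap would need the rates to differ by 0.15/0.20 = 75 points. The low-motivation rate would be 25% - 0.5 x 75% = -12.5%, which is impossible.

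**Does adjustment help?** In simulations (1,500 per setting, 20 per group, gaps of 0.5 to 1.0 SD, OR 1.65 to 2.7), the unadjusted test rejected 12 to 26% of the time. Logistic regression with motivation in the model rejected 5 to 7%. This assumes that motivation is measured without error.

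**How many covariates?** The hypothesis implies 8 + 5 = 13 people in work. Group, motivation, age, gender and criminality make five terms, or 13/5 = 2.6 events per term.

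**The case against.** The strongest reply is that the article has already dealt with the problem. It admits the lack of randomisation, names logistic regression on motivation as the remedy, collects MTW at baseline and plans the adjusted model for the same outcome at the same times. Crude and adjusted results side by side are normal in a non-randomised study. The rule on motivation follows directly after the regression sentence, so it may mean that conclusions will rest on the adjusted results. A condensed article may also leave the order of analyses to a fuller plan.

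Much of this stands, and it rules out three stronger readings. A reader might infer that the chi-square is the primary analysis. No section says so; it comes first and is given the significance question, but a primary outcome is named and a primary analysis is not. A reader might infer that the control group consists of people who declined IPS. The inclusion criterion and the Discussion make this plausible for many, but the No IPS group is never defined that way, and declining IPS is not the same as not wanting a job. A reader might take a spurious gap close to 15 points as the expected result. It needs a large imbalance combined with a strong link to employment; smaller gaps give 2 to 9 points.

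What the reply does not remove is the conflict in the current text. The tests and the rule are both stated, in the same section, and they cannot both be followed. The t-tests have no adjusted companion at all.

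**Conclusion.** The point holds in limited form. The chi-square and the t-tests break the stated rule, and the article does not say which employment analysis decides. If higher motivation makes work more likely and is more common among IPS participants, the unadjusted comparison favours IPS.

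The size of the bias cannot be fixed from the article. Over the assumed range it is about 2 to 20 points against a target of 15, with rejection of about 7 to 37% at z = 1.645, or 6 to 27% at two-sided 0.05, where 5% is intended. At the upper end, a significant chi-square would be at least as likely from motivation alone as from a real 15-point effect. At the lower end the distortion is small. It does not follow that any observed difference would be spurious, only that the chi-square could not tell the two explanations apart.

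**What to change.** - Name one decisive analysis: logistic regression of competitive employment by 12 months on group and baseline MTW, with a penalised (Firth) likelihood and no further covariates, because only about 13 events are expected. Report an adjusted risk difference with a 95% confidence interval.
- Keep the chi-square as an unadjusted description only.
- Replace the t-tests with regressions adjusted for baseline MTW and for the baseline score where one is collected. Table 1 shows no baseline TAG.
- Show the MTW distribution by group, so that readers can see how far the groups overlap.
- Word the conclusion as an association. Adjustment for one measured scale does not remove other differences between self-selected groups.
- Optionally, record at baseline whether each person wants competitive work now, and repeat the comparison among those who do. This may leave few controls.

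The cost is mainly wording, since MTW is already collected at baseline. The statistical price is a wider interval. By a linear approximation the standard error grows by sqrt(1 + d²/4): about 1% at 0.3 SD, 8% at 0.8 SD, 12% at 1.0 SD and 41% at 2 SD. With little overlap the model would have to extrapolate, and the report should say so.
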